## Abstract

**Background:**

Death rates due to hypertension in low and middle income countries are higher compared to high income countries. The present study is designed to combine life style modification and home blood pressure monitoring for control of hypertension in the context of low and middle income countries.

**Methods:**

The study is a two armed, parallel group, un-blinded, cluster randomized controlled trial undertaken within lower income areas in Kuala Lumpur. Two housing complexes will be assigned to the intervention group and the other two housing complexes will be allocated in the control group. Based on power analysis, 320 participants will be recruited. The participants in the intervention group (n = 160) will undergo three main components in the intervention which are the peer support for home blood pressure monitoring, face to face health coaching on healthy diet and demonstration and training for indoor home based exercise activities while the control group will receive a pamphlet containing information on hypertension. The primary outcomes are systolic and diastolic blood pressure. Secondary outcome measures include practice of self-blood pressure monitoring, dietary intake, level of physical activity and physical fitness.

**Discussion:**

The present study will evaluate the effect of lifestyle modification and peer support home blood pressure monitoring on blood pressure control, during a 6 month intervention period. Moreover, the study aims to assess whether these effects can be sustainable more than six months after the intervention has ended.

## Background

Data reported from the World Health Organization (WHO) showed that hypertension caused approximately 13% of annual deaths worldwide in the year of 2004. Death rates due to hypertension in low and middle income countries are higher compared to high income countries [1,2]. Based on a report by WHO's South East Asia, hypertension prevalence ranges from 8% to 40% in the region. Hypertension is also a major non communicable disease in Malaysia. It is estimated that 5.8 million people or 21% of the entire Malaysian population suffer from hypertension and there was an increasing trend over the past decade [3].

Despite availability of effective anti-hypertensive medications at affordable cost, the control of hypertension is still a major issue in both developed and developing countries in Asia [4]. Lifestyle modification which mainly includes dietary adjustment, exercise and weight management can be used as a non-pharmacological intervention in managing chronic non communicable diseases [5]. According to previous evidence, life style modification is a promising tool for prevention and control of hypertension [6-9].

Patients' non-cooperation or lack of compliance to pharmacological and non-pharmacological treatment are identified as key barriers in hypertension management [10]. A review by Glynn et al (2010) concluded that self-monitoring of blood pressure and regular follow up increased adherence to medication as well as blood pressure control. It was supported by several studies that self-management of hypertensive patients which includes home blood pressure monitoring aids in blood pressure reduction [11-13].

The present study is designed to combine life style modification and home blood pressure monitoring for control of hypertension in the context of low and middle income countries. To our knowledge, this is the first study to explore the effect of peer support home blood pressure monitoring rather than an individual based approach. The outcome from this study potentially may assist in development of future public health intervention in a resource limited setting.

## Materials/design

### Objectives

Objectives of this study are to investigate the effect of lifestyle modification and peer support home blood pressure monitoring on blood pressure control, dietary intake, physical activity and fitness during asix-month intervention period. Moreover, we aim to assess whether these effects are sustained more than six months after the intervention has ended.

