### Study tools and measurements

The following tools and measurements will be used to evaluate the effect of the intervention and compliance of the participants regarding lifestyle modification included in the intervention. The measurements will be taken at baseline, six months and twelve months for both groups.

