### Follow up and outcome measurement

The follow up will be at six months and twelve months for both intervention and control groups. The GPAQ questionnaire survey, 7 days diet history, blood pressure measurement and physical evaluation will be conducted at baseline, six months and twelve months. The log book kept by participants in the intervention group will be checked for completeness and errors after one month of the intervention and the record will be taken at three, six, nine and twelve months in order to check the compliance of self-blood pressure monitoring and home-based exercise, and whether they measured their blood pressured once a week or not.

The primary outcomes will be systolic and diastolic blood pressure measured at zero month (enrolment), six months (end of intervention period), and twelve months (maintenance period). Secondary outcome measures include some Social Cognitive Theory variables related to self-efficacy and self-regulatory such as practice of self-blood pressure monitoring, and adherence of exercise. Other secondary outcomes will be dietary intake, level of physical activity and physical fitness in term of both cardio vascular endurance and muscle strength.

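### The second objective promises evidence beyond six months after the intervention, but the last outcome visit falls exactly six months after it, with log-book checks continuing in the intervention arm

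*Protocol article*

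**What the plan says.** The second aim appears twice in the protocol article. In Objectives: "we aim to assess whether these effects are sustained more than six months after the intervention has ended". In the Discussion part of the abstract: "the study aims to assess whether these effects can be sustainable more than six months after the intervention has ended". The same part of the abstract gives the length of the intervention: "during a 6 month intervention period".

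The schedule is stated in two other places. Study tools and measurements: "The measurements will be taken at baseline, six months and twelve months for both groups". Follow up and outcome measurement: "The follow up will be at six months and twelve months for both intervention and control groups". The latter section also labels the time points of the primary outcome: "six months (end of intervention period), and twelve months (maintenance period". No later visit is described anywhere.

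Follow up and outcome measurement also deals with the log book kept by the intervention group. It is looked over after one month, and then "the record will be taken at three, six, nine and twelve months in order to check the compliance of self-blood pressure monitoring". The same sentence extends the check to exercise at home and to whether blood pressure was measured weekly. No log book is described for the control group. The Intervention section lists peer-supported home monitoring as the first of three components.

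**The concern.** There are two separate difficulties with the sustainability aim.

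- **Horizon.** The aim is set beyond six months after the end of the intervention, while the visits appear to stop at six months after it. A stated objective would then have no observation behind it.
- **Cleanness of the post-intervention period.** One arm's records of self-monitoring and exercise are still being collected for compliance during the months labelled maintenance. The protocol's own Background cites a review in which self-measurement together with regular follow-up improved both adherence and blood pressure control. By that rationale, continued checks in one arm could help to maintain a difference.

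Blood pressure at month 12 is one of the primary outcome time points, so this is not a peripheral analysis. If the objective stays as worded, a difference at month 12 could be reported as an effect lasting longer than was observed, and as one that persisted without further arm-specific study follow-up.

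**Working it through.** **Inputs**

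| Item | Value | Source |
|---|---|---|
| Claimed horizon | more than 6 months after the end | Objectives; Abstract |
| Length of intervention | 6 months | Objectives; Abstract |
| End of intervention | month 6 | Follow up and outcome measurement |
| Outcome visits, both arms | months 0, 6, 12 | Study tools and measurements; Follow up and outcome measurement |
| Log-book records, intervention group | months 3, 6, 9, 12, after a check at one month | Follow up and outcome measurement |

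**Step 1: does the schedule reach the claimed horizon?**

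Longest post-intervention observation = last outcome visit − end of intervention = 12 − 6 = 6 months.

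The objective requires more than 6, and 6 > 6 is false, so the plan's own figure is not reproduced. To meet it, a visit would have to fall after month 6 + 6 = 12. The number of scheduled outcome visits after month 12 is zero.

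Nor is a later controlled comparison in prospect. Ethical consideration says that the control groups receive the full intervention once the study is complete. If completion means the twelve-month visit, which is the last one described, the untreated comparison ends there.

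**Step 2: what arm-specific contact falls after month 6?**

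- Log-book collections after month 6: month 9 (9 − 6 = 3 months after the end) and month 12 (12 − 6 = 6 months after the end).
- Outcome visits attended by both arms after month 6: month 12.
- Collections that do not coincide with a visit of both arms: month 9 only.

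So there is one clear additional contact in the intervention arm between the end of the intervention and the final measurement. The month-12 collection comes at a visit that controls also attend.

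**Step 3: what can be said about treatment in months 6 to 12?**

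The Intervention section describes forming the peer groups, giving each group a monitor and training the participants. It does not say when the monitors are returned, if ever, or whether the groups are disbanded. It mentions six coaching sessions without dates. What is stated after month 6 is the collection of log-book records as a compliance check. The text therefore establishes continued follow-up of self-monitoring and exercise. It does not establish continued delivery of a component.

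**The case against.** The strongest reply is that this is a slip at a boundary. The schedule is stated plainly, month 6 is labelled as the end of the intervention, and any careful reader sees a six-month maintenance period. Removing two words in two sentences would bring the horizon into line. That stands as a description of how small the repair is. It does not remove the contradiction, which appears in both the objective and the abstract.

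The second reply is that continued self-measurement and exercise are part of what is meant by a sustained effect. The practice of self-monitoring and adherence to exercise are listed as secondary outcomes, and records at months 9 and 12 are how that behaviour is observed. This also has force, and the documents give no evidence that a log-book check changes blood pressure at month 12. It remains true that the check is described for one arm only, so the wording of the objective should disclose it.

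A reader might infer three stronger things that the document does not support:

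- **That an intervention component is still running to month 12.** The article does not say whether peer support or the shared monitors stop at month 6, and its own label places the end of the intervention there. Continued delivery is a possible reading, not a stated fact.
- **That there are two arm-only contacts in the maintenance period.** Both arms attend at month 12, so only month 9 is clearly additional.
- **That the twelve-month comparison cannot address sustainability at all.** It can address it at six months after the intervention period. What it cannot support is a claim beyond that.

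**Conclusion.** The point holds in a limited form. The stated horizon and the schedule conflict: the objective asks for more than six months after the end, and the design gives exactly six. Separately, the maintenance period is not free of arm-specific study follow-up, because log-book compliance checks continue in the intervention group, with one additional contact at month 9.

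The defect lies in what may be concluded at month 12. It does not touch the six-month comparison or the sample size. It deserves correction because it concerns a primary outcome time point.

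The conclusion assumes nominal visit times and takes the protocol's own label of month 6 as the end of the intervention. How far months 6 to 12 differ from a period without intervention depends on what happens to the peer groups and monitors, which the article leaves open.

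**What to change.** Reconcile Objectives and the abstract with Study tools and measurements and Follow up and outcome measurement. A wording that fits the schedule:

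> The second objective is to estimate the between-arm difference at twelve months, that is, six months after the end of the six-month intervention period, with log-book compliance checks continuing in the intervention group.

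Use the same statement in the abstract, and limit the sustainability conclusion to it.

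The cost is two or three sentences and a slightly narrower claim. No visit is added, and no analysis or sample size changes.

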### Study design and setting

The study is a two armed, parallel group, un-blinded, cluster randomized controlled trial undertaken within lower income areas in Kuala Lumpur. There are six community housing complexes in the study area. Of these four housing complexes will be randomly selected and allocated (1:1) to the intervention and control arm (Figure 1).

**Figure 1 F1:**
[figure not shown]
Flow of participants in the intervention and control arm

The intervention group will receive training on self-measurement of blood pressure, health coaching on healthy diet, training for indoor exercise activities and the use of Body Mass Index (BMI) calculator. Participants in the control group will receive a BMI calculator and a pamphlet developed by the study team which includes brief information on hypertension, healthy diet and physical activity.

Residents of the selected community housings who were diagnosed as having (stage 1 to stage 3) hypertension by medical professionals will be recruited as participants for the study. The potential participants will be identified based on the household survey data which was carried out by the 'PARTNER' study team from the University of Malaya. This survey was a cross-sectional design and conducted between February to November 2012. Altogether, 833 households were recruited from total 4726 households of four Community Housing Projects by using simple random sampling method. From 833 households, 431 individuals with hypertension were identified.

Inclusion and exclusion criteria of the study are as follows.

#### Inclusion criteria

Adults aged 18 years and above will be eligible for the study if they have been diagnosed as having hypertension (stage 1 to 3) by medical professionals, Malaysian citizen, able to speak Malay (national language) or/and English, willing to participate in all aspects of the intervention and fit to do exercise. Participants who can do daily activities without limitations are defined as "Fit to do exercise". The potential participants will be screened by Physical Activity Readiness Questionnaire (PAR-Q) whether they are fit to do exercise or need further consultation with physician[14].

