### Sample size calculation and recruitment

The sample size was calculated by assuming p < 0.05 as the significance level, 80% power and 1 to 1 as the ratio of unexposed to expose in sample. The calculation was carried by using the OpenEpi version 2.3.1 [15]. On the assumption of an SD of 15 mmHg and 30% drop out, a sample size of 160 participants per group is required to detect the effect size of systolic blood pressure 5.4 mm Hg. The effect size used to calculate the sample size was based onthe result of a previous similar study[16].

Universal sampling method will be used to recruit the study participants. The 431 residents of the selected community housing complexes who were diagnosed as (stage 1 to 3) hypertension will be invited to the study. We will take all participants which fit with inclusion criteria and willing to participate to the study so that actual participants may be more than calculated sample size.

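### The entry criterion on willingness for the intervention may select differently in the two arms, because nothing places consent and eligibility before disclosure of the allocation

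*Protocol article*

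**What the plan says.** **Design and allocation.** Under Study design and setting: "The study is a two armed, parallel group, un-blinded, cluster randomized controlled trial". The same section covers selection and assignment in one sentence: "Of these four housing complexes will be randomly selected and allocated (1:1) to the intervention and control arm".

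**Who is approached.** The text after Figure 1 states: "Residents of the selected community housings who were diagnosed as having (stage 1 to stage 3) hypertension by medical professionals will be recruited". Candidates come from a 2012 household survey: "The potential participants will be identified based on the household survey data", and "From 833 households, 431 individuals with hypertension were identified". Sample size calculation and recruitment adds: "The 431 residents of the selected community housing complexes who were diagnosed as (stage 1 to 3) hypertension will be invited to the study". Everyone who is eligible and willing is taken.

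**The criterion.** Inclusion criteria requires residents to be "willing to participate in all aspects of the intervention and fit to do exercise". It is stated once, for both arms.

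**What each arm involves.** Intervention and Follow up and outcome measurement describe peer groups sharing a monitor, log books checked for weekly readings, six dietary coaching sessions, and exercise training with a recommended weekly minimum of 150 minutes. Controls receive a pamphlet and a BMI calculator during the trial. Ethical consideration promises them all components after the study ends.

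**Handling of imbalance.** Data management and analysis adjusts by MANOVA only if group characteristics are found to differ.

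**The concern.** Randomising complexes makes the resident populations comparable in expectation. It does not make the people who enrol comparable if enrolment happens after the arm is known and the act of enrolling means different things in each arm.

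The criterion is tied to the content of one arm. In a complex known to be in the intervention arm, agreeing to every aspect is a substantial commitment, and residents who do not want it are screened out. In a complex known to be a control, the same sentence screens out few people, because those activities are not on offer until after the twelve-month measurement. The enrolled intervention group could then be more motivated than the enrolled control group for reasons unrelated to treatment.

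Willingness to attend coaching, exercise and self-monitor plausibly predicts adherence and so the course of blood pressure. If so, part of any between-arm difference in the primary outcomes would reflect who enrolled. Conditional adjustment for measured characteristics cannot remove selection on unmeasured motivation, and with two complexes per arm randomisation offers little balance to begin with.

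**Working it through.** **1. Order of steps.** Set side by side, Study design and setting selects and allocates complexes in one step. The text after Figure 1 recruits residents of the selected complexes, and the recruitment section invites "The 431 residents of the selected community housing complexes". The natural reading is allocation first, then invitation. No sentence says when allocation is drawn or disclosed relative to consent, and no sentence says that residents or recruiters are unaware of the arm. Figure 1 is not shown.

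**2. What the criterion then does.** Two cases follow.
- *Willingness judged before the arm is known:* the same filter acts in all four complexes. Generalisability narrows, and the comparison is not biased by it.
- *Willingness judged after the arm is known:* the filter is strong in intervention complexes and weak in control complexes. The comparison may be biased.

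**3. The plan's own figures, for scale.** With SD 15 mmHg, difference 5.4 mmHg, two-sided 5% and 80% power:

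n = 2 × (1.960 + 0.842)² × 15² / 5.4² = 121.1, so 122 per group.

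122 × 1.30 = 158.6, so 159, which agrees with the stated 160. This point does not rest on the sample size. The 5.4 mmHg serves only as a yardstick.

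**4. Room for differential uptake.** 320 / 431 = 74.2%. About 26% of the listed residents can be lost and the target is still met. That margin must also cover every other reason for non-entry, such as failing the exercise-readiness screen, language, citizenship, pregnancy, other trials, planned moves and non-contact.

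**5. Illustration (assumptions, not documented facts).** Let latent willingness be standard normal, with correlation ρ to systolic pressure (SD 15 mmHg), and let the most willing fraction p enrol. The mean pressure of those enrolled is displaced by

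ρ × 15 × φ(c) / p, with c = Φ⁻¹(1 − p).

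The spurious difference is the displacement in the intervention arm minus that in the control arm. Example with uptake 69% v 79% and ρ = 0.1:
- Intervention: φ(c)/p = 0.3528 / 0.69 = 0.5113.
- Control: φ(c)/p = 0.2882 / 0.79 = 0.3648.
- Difference: 0.1 × 15 × (0.5113 − 0.3648) = 0.22 mmHg.

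| Uptake, intervention v control | ρ = 0.1 | ρ = 0.2 | ρ = 0.3 | Share of 5.4 mmHg |
|---|---|---|---|---|
| 74% v 74% | 0 | 0 | 0 | 0% |
| 69% v 79% | 0.22 | 0.44 | 0.66 | 4% to 12% |
| 64% v 84% | 0.44 | 0.88 | 1.33 | 8% to 25% |
| 59% v 89% | 0.67 | 1.34 | 2.01 | 12% to 37% |

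The values are absolute sizes. The sign follows the sign of ρ, which the documents do not give.

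**6. Check against the planned arm size.** Assume the 431 split evenly, 215.5 per arm. The three unequal scenarios then give 149, 138 and 127 intervention participants, all short of 160. Holding the intervention arm at 74.2% (160 people) and raising control uptake to 90% gives φ(c)/p of 0.4354 and 0.1950. The difference is 15 × 0.2404 × ρ = 0.36 to 1.08 mmHg for ρ = 0.1 to 0.3, or 7% to 20% of 5.4. The upper end of the table therefore goes with an intervention arm that misses its target.

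**The case against.** Several points count against a strong reading.

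- **Timing is inferred.** A reader might conclude that residents are certainly approached in complexes whose arm is already known. The article does not say so. Its text order is not reliably chronological: selection of complexes is in the future tense, while the survey that supplied the 431 names is already done. Un-blinded conduct does not settle what is disclosed at consent. This stands, and the point is conditional for that reason.
- **The criterion is common to both arms.** Fitness to exercise is also required of everyone, which suggests one eligibility standard. This stands as far as intent goes, but identical wording does not ensure identical effect once the arm is known.
- **Controls get everything later.** The criterion is therefore not empty for controls. This stands in part: the commitment is deferred until after the last outcome measurement.
- **Recruiters do not choose candidates.** The pre-existing list and invitation of everyone on it largely remove selective identification. This stands, but it does not touch selection through consent or the willingness judgement.
- **A single damaging figure is tempting.** Suppose 40% of residents were unwilling and would do 5 mmHg worse, with 60% enrolling in the intervention arm and 90% in the control arm. Then 30/90 = 33% of controls would be unwilling types, and 0.333 × 5 = 1.7 mmHg. None of those inputs is in the documents, and on an even split 60% of 215.5 is about 129 intervention participants, not 160. The figure should not be relied on.
- **Condensed article.** The sequence of consent and allocation could sit in a fuller protocol. That would excuse silence on the sequence alone. It does not excuse an entry criterion, stated here, that is tied to the content of one arm in an open cluster trial.

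**Conclusion.** The point holds in conditional form. As written, the criterion may select differently in the two arms if willingness is judged after the arm is known, and the article neither excludes that nor places consent first. The documents do not show that such selection will occur, and they do not fix its size or direction. The range of roughly 0.2 to 2.0 mmHg (4% to 37% of the target effect) rests on three assumptions: uptake gaps of 10 to 30 percentage points, correlations of 0.1 to 0.3, and a normal selection model. With equal uptake and the same selection in both arms it is zero. The case for acting rests on the mechanism and the low cost of closing it off, not on any one figure in that range.

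**What to change.** 1. Reword the willingness criterion so that it is arm-neutral: willing to take part whichever group the complex is assigned to.
2. Complete eligibility screening, consent and baseline measurement of the listed residents in all four complexes before the allocation is drawn or disclosed, and state that order in the protocol.

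The list of 431 already exists, so no new sampling is needed. The cost is a re-ordering of field steps and some delay between baseline and the start of the intervention. That delay is not trivial to schedule, since baseline includes dietitian-led diet histories and fitness tests as well as blood pressure.

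If consent already precedes disclosure, one sentence saying so is enough for the second item, and only the criterion's wording needs changing. Reporting uptake by complex would help readers judge the result, but it is a reporting matter and not part of this correction.
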